## 12. Definition of endpoints

### 12.1 Primary endpoints

#### 12.1.1 Renal function deterioration

Composite events of each event occurring 12 weeks after the start of treatment (see “10.4.1 Event – Renal function deterioration”) are set as renal function deterioration. The number of days until occurrence is calculated, with 12 weeks after the start of treatment as the starting point.

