#### 12.1.2 CVD event

Composite events of each event occurring 12 weeks after the start of treatment are set as the CVD event. The number of days until occurrence is calculated, with 12 weeks after the start of treatment as the starting point.

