### 12.3 ERI

The following five indices are considered new candidates for the ESA response indices (ERIs) to be investigated.

- ERI-1A (index according to one time point at 12 weeks)

$$\frac{\text{DA administered dose 12 weeks after the start of treatment (}\mu\text{g)}}{\text{Hb concentration 12 weeks after the start of treatment (g/dL)} \times \text{weight 12 weeks after the start of treatment (kg)}}$$

- ERI-1B (index according to one time point at 12 weeks)

$$\frac{\text{DA administered dose 12 weeks after the start of treatment (}\mu\text{g)}}{\text{Hb concentration 12 weeks after the start of treatment (g/dL)}}$$

- ERI-2A (index that considers the cumulative administered dose up to 12 weeks and changes in Hb concentration)

$$\frac{\text{Total DA administered dose up to 12 weeks after the start of treatment } (\mu\text{g})}{\text{Amount of change} \times \text{weight at 12 weeks (kg)}}$$

- ERI-2B (index that considers the cumulative administered dose up to 12 weeks and changes in Hb concentration)

$$\frac{\text{Total DA administered dose up to 12 weeks after the start of treatment } (\mu\text{g})}{\text{Amount of change}}$$

- Change in Hb concentration (changes in Hb concentration up to 12 weeks)

$$\text{Hb concentration at 12 weeks (g/dL)} - \text{prior Hb concentration (g/dL)}$$

A similar index is created for the ERI index from the Hb concentration and darbepoetin alfa administered at 16 weeks and at 24 weeks in addition to that at 12 weeks, and the associations between these indices and event occurrence are also investigated. When the ERI index at 12 weeks favorably predicts event occurrence, then whether the ERI index composed of the values at week 10, 8, 6, 4, and 2 favorably predicted the event occurrence is confirmed in order.

New indices are further explored if no associations between these index candidates and renal function deterioration or CVD events were found.

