#### 13.2 Analysis set

The following groups are defined as the analysis sets. The acceptance or rejection of individual patients in each group is determined prior to the fixing of the data as needed. The main analysis set for efficacy evaluation is set as the “efficacy analysis set,” but a similar efficacy analysis is implemented for “ACS.”

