### 13.2.2 Efficacy analysis set

The group excluding the following patients from the safety set is defined as the efficacy analysis set.

- Those who were ineligible after registration
- Those who discontinued darbepoetin alfa administration within 12 weeks after the start of treatment
- Those who do not have a single DA administration record 12 weeks after the start of treatment
- Hb concentration measurements are not obtained at the start of treatment and at 12 weeks

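### The week 2–10 ERI look-back inherits the week-12 origin and analysis set, so it can compare early with week-12 ERIs but gives no prediction, event rates or cut-offs from when the early index is known

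*Protocol*

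**What the plan says.** Five response indices are built on week-12 values (Protocol 12.3). If the week-12 version predicts well, the plan then checks in turn "whether the ERI index composed of the values at week 10, 8, 6, 4, and 2 favorably predicted the event occurrence". No separate start of follow-up or population is given for these earlier versions.

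The time-to-event endpoints are fixed at week 12:
- Renal (12.1.1): "Composite events of each event occurring 12 weeks after the start of treatment".
- CVD (12.1.2): "Composite events of each event occurring 12 weeks after the start of treatment are set as the CVD event", and "The number of days until occurrence is calculated, with 12 weeks after the start of treatment as the starting point". The renal endpoint has the same origin.

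The main set (13.2.2) excludes, among others, "Those who discontinued darbepoetin alfa administration within 12 weeks after the start of treatment" and "Those who do not have a single DA administration record 12 weeks after the start of treatment", and also patients without the start and week-12 Hb. The compliance set (ACS, 13.2.3) is a subset of this set, so it carries the same conditions.

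Under 10.4.1, the 50% eGFR decline is measured against mean eGFR from the start of treatment to week 12.

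**The concern.** For a week-12 index, week 12 is the natural origin. For a week-2 index it is not. Whether a patient is analysed then depends on the ten weeks after the index is known, and events in those weeks are not counted. Those removed have died, stopped the drug or gone unmeasured, and these reasons may well relate to response and risk.

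The look-back bears on whether low response can be recognised before week 12. Section 13.3.1 goes on from ROC curves to cut-offs, Kaplan-Meier plots and annual event rates. For an early ERI, those would describe patients who later proved to be still treated and measured at week 12. That group cannot be identified when the index becomes available.

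**Working it through.** **1. The plan's own figure.** Section 13.1 gives 2,000 patients, two years, 13.1 events per 100 person-years and a 95% interval of 480–568 events.
- Expected count: 2,000 × 2 × 0.131 = 524.
- Poisson limits: 524 ± 1.96 × √524 = 479.1 to 568.9.

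The stated interval reproduces, so the rate can be used. The protocol does not say clearly whether it covers renal events, CVD events or each separately.

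**2. Events between the early index and week 12.** Assume a constant hazard, first events only, and 2,000 patients at risk at week k. The weekly hazard is λ = 0.131 / 52.18 = 0.00251.
- Uncounted: 2,000 × (1 − exp(−λ(12 − k))).
- Total to week 96: 2,000 × (1 − exp(−λ(96 − k))).

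| Index week k | Uncounted | Total k to 96 | Share |
|---|---|---|---|
| 2 | 49.6 | 420.4 | 11.8% |
| 4 | 39.8 | 412.5 | 9.6% |
| 6 | 29.9 | 404.5 | 7.4% |
| 8 | 20.0 | 396.5 | 5.0% |
| 10 | 10.0 | 388.4 | 2.6% |

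These are probably upper figures for renal events. Section 5.2 excludes patients with dialysis or transplant planned within 24 weeks of registration. Treatment starts within 8 weeks of registration (5.1), so week 12 falls at most 8 + 12 = 20 weeks after registration, inside that window.

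**3. Effect of the exclusions.** The protocol gives no figure for leaving before week 12, so this step rests on assumptions, tested by simulation:
- a standard normal week-2 index with event hazard ratio 1.3 or 1.5 per SD;
- log-normal frailty (SD 0.5) shared between events and leaving;
- 5–15% leaving between weeks 2 and 12, with rate ratio 1.0 or 1.5 per SD of the index.

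The comparison is all patients from week 2 against those event-free and on drug at week 12. Section 13.2.2 does not require patients to be event-free, so this is an approximation.

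| Quantity | Result |
|---|---|
| Events after week 2 lost, with leaving | 17–29% |
| Fall in top-quarter risk difference, 84 weeks on both sides, no leaving | about 1% or less |
| Same, with 5–15% leaving | about 2–6% in most settings; up to about 12% at 15% leaving, ratio 1.5 |
| Change in AUC, 84 weeks on both sides | at most about 0.007 (for example 0.578 to 0.572) |

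**The case against.** The strongest reply is that the look-back is conditional. It runs only once the week-12 ERI has predicted well, and then steps back week by week. That reads as asking whether an earlier index can replace the week-12 one, for which the same patients, events and origin are the fair basis. This stands, and it is why the common-origin comparison should remain.

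A reader might go further and infer that the look-back cannot show how well an early index predicts. The documents do not support that. The analysis validly ranks risk after week 12 among patients still treated, and in the simulation the planned AUC barely moves.

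A reader might also put the loss of separation at 9–19%. That comes from comparing weeks 2–96 (94 weeks) with weeks 12–96 (84 weeks). The shorter window alone produces 8–9% with nobody leaving, so most of it is not selection.

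Two further replies carry some weight. The 50% eGFR component is not defined before week 12 as written, so an earlier origin needs more than a new date; dialysis, transplant, eGFR at or below 6 and all CVD events do not depend on that baseline. The work is also exploratory, with detail left to the SAP (13.3). But the protocol itself fixes origin and set at week 12 without exception, and section 2 makes proposing indices and cut-off values a study aim.

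**Conclusion.** The point holds in a limited form. As written, the week 2–10 ERIs are judged only on events after week 12, in patients selected by what happens after the index is known. This answers whether an early ERI does as well as the week-12 ERI in patients still treated. It does not give prediction, absolute rates or cut-offs from the date of the early index in all who have it.

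The size is moderate: about 50 uncounted events for the week-2 index, falling to about 10 for week 10, at a constant planning rate. Removal of patients who leave comes on top, in a number the protocol does not state. On the assumptions tested, ranking is nearly unaffected. The consequence lies in lost events and in whom the rates and cut-offs describe. The week-12 ERI analysis is not affected.

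**What to change.** Keep the common week-12-origin comparison of early with week-12 ERI in the efficacy set. Add to 12.3 and 13.3.1 that each week-k ERI (k = 2, 4, 6, 8, 10) is also evaluated from its own landmark:
- **Set:** at least one darbepoetin alfa dose by week k, Hb at the start and at week k, and no earlier event of the type analysed, whatever happens afterwards.
- **Follow-up:** events counted from week k, over a stated horizon equal for all k.
- **Renal composite:** dialysis, transplant and eGFR at or below 6 counted from week k. Include the 50% eGFR decline with mean eGFR up to week k as baseline, noting that it rests on fewer values.
- **Reporting:** early-ERI cut-offs and event rates come from this analysis.

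The cost is wording and five extra runs. Section 10.1.3 already collects Hb, weight, dosing and dated events, and 8.2 keeps patients who stop darbepoetin alfa under observation to week 96. The downside is that sets, origins and the eGFR baseline differ between weeks; the retained common-origin comparison covers the need for a like-for-like contrast.

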## 13.3 Analysis items / methods

As a general rule, categorical data calculate frequencies and percentages, and continuous values are summarized with the summary statistical values of the number of patients, average value, standard deviation, minimum value, median value, and maximum value.

A significance level is not set because there are no hypotheses to be verified that are set in this research, but a two-sided P-value of 5% is set when using statistical test methods in an exploratory manner.

Details on analyses not recorded in this research protocol are described in the “Statistical Analysis Plan”

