### 13.3.1 Renal function deterioration, CVD event investigation

A proportional hazards model that includes the following covariates is applied, and the factors that affect event occurrence are investigated. Covariates are added or decreased as required for the investigation of the model. Hb concentration values at each measurement time point up to 24 weeks instead of week 12 of administration are also investigated. The presence of diabetic complications, arteriosclerosis, and chronic inflammation should also be considered as stratification factors. These analyses are used to investigate the prediction equation for event occurrence from the covariates.

- Age; sex; weight; eGFR, serum albumin, hemoglobin concentration, high-sensitive CRP, NT-pro BNP, folic acid, vitamin B12, serum iron, serum ferritin, and TSAT 12 weeks after the start of treatment; the presence of diabetic complications, arteriosclerosis, chronic inflammation, malignant tumor complications, hemorrhagic lesion complications, collagen disease and rheumatic disease complications, concomitant immunosuppressant or steroid use, and other myelosuppressive factors; and the darbepoetin alfa administered dose (total administered dose, administered dose 12 weeks after the start of treatment).

Next, the cut-off values of each ERI are gradually increased from the minimum value to the maximum

value; a time-dependent ROC curve of the survival time data with censoring is created, and the AUC is compared. If the cut-off value is set from the ROC curves of each obtained ERI, then these are divided into two groups at the cut-off value, Kaplan-Meier plots are created, and the annual event occurrence rate (human-year method) and 95% confidence intervals are estimated. The cut-off values of the ERIs may also be investigated using the cross-validation method, if considered useful.

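### The ERI search makes 30 looks and, only after a null result, extends to further indices in the same data with no closed list, stopping point or required validation

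*Protocol*

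**What the plan says.** Protocol section 12.3 opens the search with a fixed list: "The following five indices are considered new candidates for the ESA response indices (ERIs) to be investigated". It then widens the list in time: "A similar index is created for the ERI index from the Hb concentration and darbepoetin alfa administered at 16 weeks and at 24 weeks". Each version is related to two outcomes, renal function deterioration and CVD events. If nothing emerges, the section continues: "New indices are further explored if no associations between these index candidates and renal function deterioration or CVD events were found". No number, form or end point is given for these further indices, and no separate data are set aside for them.

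Section 13.3 gives the inferential frame. It states first that "A significance level is not set because there are no hypotheses to be verified that are set in this research", and then that "a two-sided P-value of 5% is set when using statistical test methods in an exploratory manner". No multiplicity rule is stated.

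Section 13.3.1 compares the ERIs by the AUC of time-dependent ROC curves, for which "the cut-off values of each ERI are gradually increased from the minimum value to the maximum" value. Cross-validation appears once. It concerns the cut-offs only, and its use is left to judgement.

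Section 1 gives the purpose as determining a new ERI related to poor renal and cardiovascular prognosis. Section 2 adds the intention to put forward measures of low ESA response, with thresholds, that suit Japanese practice.

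**The concern.** The search is asymmetric. When a listed candidate looks associated with an outcome, it can be taken forward. When none does, more candidates are built and examined on the same patients and the same events. The prespecified, clinically motivated indices have failed by then, so a chance association is at its most likely to be promoted. Nothing that the protocol requires stands between the search and the proposal of an index. The optional cross-validation would not correct for the choice of index or of time point even if it were used.

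Two things are at stake. The AUC of the winning index will be optimistic, because index, time point and cut-off are all chosen on the data that are used to report it. And an index with no real relation to outcome could be offered for use in practice.

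**Working it through.** **The plan's own figure.** The protocol states no error rate for the search. Its only calculated figure is the event count in section 13.1, and this reproduces: 2,000 × 2 × 0.131 = 524, and 524 ± 1.96 × √524 = 479.1 to 568.9, against the stated 480–568. The figures below do not depend on it.

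**Inputs from the protocol**
- Indices: 5 (section 12.3).
- Time points: 3, since the indices are repeated "at 16 weeks and at 24 weeks in addition to that at 12 weeks" (section 12.3).
- Endpoints: 2 (section 12.3).
- Threshold: two-sided 5% where tests are used (section 13.3).

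**Assumptions**
- Association is judged at that 5%. Section 12.3 does not define it.
- The correlation among the 15 index-by-time versions is not given, so a range is shown.
- No index is truly related to either endpoint.

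**Step 1: independent tests, as an upper reference.** The chance of at least one false association in k tests is 1 − 0.95^k.
- Week 12 only, k = 5 × 2 = 10: 1 − 0.95^10 = 40%.
- All listed candidates, k = 5 × 3 × 2 = 30: 1 − 0.95^30 = 78.5%.

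**Step 2: equal correlation among the 15 versions, endpoints independent (Monte Carlo on normal score statistics)**

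| Correlation | At least one false association in 30 looks |
|---|---|
| 0 | 79% |
| 0.3 | 71% |
| 0.5 | 59% |
| 0.7 | 45% |
| 0.8 | 36% |
| 0.9 | 27% |

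At perfect correlation, which the differing formulas rule out, the two endpoints alone would give 1 − 0.95² = 9.75%.

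**Step 3: correlations produced by the five formulas.** Cohorts of 2,000 were simulated with assumed Hb, dose and weight distributions. Within-patient correlation of Hb and dose was varied from 0.5 to 0.9, endpoint correlation was 0 or 0.3, and indices were used raw or ranked.
- Week 12 only: 27% to 30%.
- Weeks 12, 16 and 24: 49% to 61%.

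A separate simulation tested the indices directly against events (1,800 patients, 24% with each event). It gave 29% at week 12 and 51% over the three time points.

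**Step 4: further indices after a null result.** If f is the chance after the listed candidates, m new indices unrelated to the old ones and to each other give 1 − (1 − f) × 0.95^(2m).
- Five new indices: 1 − (1 − 0.593) × 0.95^10 = 76% at correlation 0.5, and 1 − (1 − 0.266) × 0.95^10 = 56% at 0.9. The simulated cohorts give 69% to 76%.
- Ten new indices: 85% at correlation 0.5 and 74% at 0.9.
- Ten new indices as correlated with the rest as the listed ones are with each other: 72% at 0.5, 43% at 0.8 and 30% at 0.9.

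The increase therefore depends strongly on how different the new indices are.

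**The case against.** The strongest reply is that the protocol claims no error control. Section 13.3 says that there is no hypothesis to verify, and sections 0.2 and 13.1 describe a search. The extension to new indices is announced in advance. All of this stands: no familywise claim is broken, and this is not a confirmatory alpha breach. It does not answer the risk in carrying a search result into practice without required validation.

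Second, the percentages rest on a decision rule that the protocol does not state. Association is never defined as P < 0.05, and the planned methods are covariate-adjusted proportional hazards models and AUC comparison. This also stands, which is why the figures are conditional. Any valid test at 5% has the same size, so what the choice of method can change is mainly the correlation, and that is covered by a range.

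Third, multiplicity and optimism correction are often placed in the SAP, which was not available here. That is fair as to detail. But the protocol itself fixes the trigger for further indices, leaves the set open, and makes cross-validation optional and limited to cut-offs.

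Four stronger readings are tempting and not supported:
- **The search runs until an index is associated.** The text says that new indices are explored. It states no stop, but also no such condition.
- **The protocol cannot return a null result.** Its own wording allows for finding none among the listed candidates, and nothing forbids reporting that.
- **Most studies with no true ERI would yield one.** The listed candidates give anything from 27% to 79%, depending on a correlation that the protocol does not give.
- **The look-back to weeks 10, 8, 6, 4 and 2 is offered as independent confirmation.** It reads naturally as a check in sequence of how early the index works.

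**Conclusion.** The point holds as a weakness in how the search is closed and validated. Section 12.3 sets up 30 looks and sends only a null result on to an open set of further indices in the same data. The only validation mentioned is optional and covers cut-offs alone. With association judged at two-sided 5% and no true effect, the listed candidates produce at least one false association in about 50% to 60% of simulated cohorts. The range is 27% (correlation 0.9) to 79% (independence), so even the lowest value is more than five times 5%. Each new index raises it, by little if it resembles the old ones and by much if it does not.

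These figures rest on the assumed threshold and on assumed Hb, dose and weight distributions. They leave out the repeat in the administration algorithm compliance set, the covariates that may be added or dropped, and the scan over cut-offs.

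**What to change.** In sections 12.3 and 13.3.1:
- Treat the five listed indices at weeks 12, 16 and 24 as a closed candidate set.
- Report each AUC with a bootstrap or cross-validation optimism correction that repeats the whole search: index, time point and cut-off.
- Judge the best candidate against a permutation-maximum reference. Follow-up times and event indicators are permuted jointly against the index data, the search is repeated, and the largest AUC deviation is kept.
- If no candidate stands out, report that no association was demonstrated for the prespecified ERIs, with confidence intervals. Do not conclude that none is related to outcome.
- Label any index built afterwards as post hoc and hypothesis-generating, and do not propose it for practice without external validation.

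The permutation maximum is preferable to Bonferroni because it uses the correlation. At 0.05/30 = 0.00167 per test, the overall chance falls to 3.9% at correlation 0.5 and 2.2% at 0.8, which is needlessly strict.

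The cost is a change of wording, some computing time and less favourable reported AUCs. No data collection changes.

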### 13. Statistical analysis

#### 13.1 Rationale for the sample size design

The objective of this research is to clarify the actual conditions of low ESA response cases in Japan, investigate factors related to low ESA response cases, and search for new ERIs. Therefore, in consideration of securing data for each type of exploratory analysis, a sample size of 2,000 was set as the scale of research where evaluations of low ESA response cases were thought to be possible.

The TREAT trial conducted internationally reported that renal events (end-stage renal failure or death) in the darbepoetin alfa group and the two-year occurrence rate of CVD events was approximately 23%–24%. If the event occurrence rate was set as 13.1 / 100 people/year from this result, then the number of events observed in two years with a sample size of 2,000 would be 480–568 patients at a 95% confidence interval, which is thought to be a sufficient number of events for the planned analyses.

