#### 11. Sample size and research period

##### 11.1 Sample size

The sample size is 2,000 patients.

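### The 480–568 events in section 13.1 keep patients at risk after their event; the protocol's own rate gives about 461 first events in two years (95% about 424–498)

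*Protocol*

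**What the plan says.** Section 11.1 fixes the size of the study: "The sample size is 2,000 patients". Section 13.1 first justifies this by the need for enough data for the exploratory analyses, and then checks it against an event count. From a cited international trial of darbepoetin alfa it takes a renal outcome, described as "renal events (end-stage renal failure or death"), together with a cardiovascular one, and reports that "the two-year occurrence rate of CVD events was approximately 23%–24" per cent. It turns this into a rate: "If the event occurrence rate was set as 13.1 / 100 people/year from this result". Applying that rate to the whole cohort, it concludes that "the number of events observed in two years with a sample size of 2,000 would be 480–568 patients at a 95% confidence interval". It judges that number adequate for the planned analyses.

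Sections 12.1.1 and 12.1.2 define both primary endpoints as composites occurring from week 12. For the renal endpoint: "The number of days until occurrence is calculated, with 12 weeks after the start of treatment as the starting point"; the CVD endpoint is timed in the same way. Section 13.3.1 analyses both with proportional hazards models, time-dependent ROC curves, Kaplan-Meier plots and person-year rates.

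**The concern.** Two adjoining sentences of section 13.1 do not agree. A two-year occurrence of 23%–24% in 2,000 patients means 460–480 patients with an event, yet the stated range is centred on 524, or 26.2% of 2,000. Its limits correspond to 24.0% and 28.4%, so the whole range lies at or above the top of the cited occurrence.

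The event count is the figure that section 13.1 offers as reassurance for a long list of analyses: 23 listed covariates, five response indices, further time points and a search for cut-offs. If the count is too high, the information expected for that work is overstated by the same proportion.

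**Working it through.** **Inputs, all from section 13.1:** N = 2,000; two-year occurrence 23%–24%; rate 0.131 per person-year; two years; stated range 480–568.

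**1. Where 13.1 comes from.** Under a constant hazard, rate = −ln(1 − risk)/2. At 23%: −ln(0.77)/2 = 0.1307. At 24%: −ln(0.76)/2 = 0.1372. The protocol's rate is thus the exponential conversion of 23%.

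**2. Reproducing the stated range.**
- Mean: 0.131 × 2,000 × 2 = 0.131 × 4,000 = 524.
- Poisson 95%: 524 ± 1.96 × √524 = 479.1 to 568.9. The whole numbers inside these limits run from 480 to 568, exactly as stated.
- A binomial interval with p = 0.262 gives about 485–563 and does not match.

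The figure therefore rests on 4,000 person-years with nobody leaving the risk set.

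**3. Counting each patient once.** The text counts patients, and each endpoint is a time to occurrence, so a patient contributes at most one event per endpoint.
- Two-year risk: 1 − e^(−0.131 × 2) = 1 − e^(−0.262) = 0.2305.
- Expected patients: 2,000 × 0.2305 = 461.
- Binomial 95%: 461 ± 1.96 × √(2,000 × 0.2305 × 0.7695) = 424 to 498.
- Person-time at risk: 461/0.131 ≈ 3,519 years, not 4,000.

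**4. Directly from the cited occurrence.**

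| Two-year risk | Expected | 95% interval |
|---|---|---|
| 23% | 460 | 423–497 |
| 24% | 480 | 443–518 |

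**5. Size of the error.** 524/461 = 1.137, about 14% too high. Against 480, 524/480 = 1.092, about 9%.

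**6. The window the endpoints use.** Time runs from week 12, and scheduled observation ends at week 96 (section 8.1), which leaves 84 weeks or 1.61 years. 1 − e^(−0.131 × 1.61) = 0.190, so about 380 of 2,000 patients, before any exclusion from the efficacy analysis set (section 13.2.2).

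**7. Follow-up after week 96.** Sections 10.1.4 and 11.2 survey every patient 96 weeks after the last registered patient starts, so earlier registrants are followed longer. Registration closes on 31 March 2016 but opens on an unspecified approval date, so its length has to be assumed. With uniform registration over A years, the expected count from week 12 to the survey is 2,000 × [1 − e^(−0.131 × 1.61) × (1 − e^(−0.131A))/(0.131A)].

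| A (assumed, years) | Expected events |
|---|---|
| 0.5 | 432 |
| 1 | 482 |
| 1.5 | 529 |
| 2 | 575 |

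**The case against.** The strongest reply is that little depends on the figure. Section 13.1 sets 2,000 on general grounds and uses the event count only as a plausibility check. Section 13.3 says there is no hypothesis to verify, and no power or precision target is given. With 23 listed covariates, 461 events are about 20 per covariate (461/23), and even 380 are about 16.5. This stands: no planned analysis is shown to work at 524 and fail at 461.

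A reader might infer that the study's final event total is overstated. The documents do not support that. With the simultaneous survey, assumed registration periods of 1 or 1.5 years give totals inside 480–568, and 2 years gives one above it. Only the sentence about two years is shown to be wrong.

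A reader might also infer that the source's renal rate is an upper bound because it includes death. That does not follow either. The trial's renal composite (section 10.4.1) leaves out death, but it adds a 50% fall in eGFR and an eGFR of 6 or below. The net direction cannot be read from the documents.

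Finally, 460–480 is a range of expected counts and 480–568 is a 95% interval, so the two should not be set against each other as if alike. The comparable intervals, 424–498 and 443–518, both overlap the stated one. This also stands: the error lies in the centre and the upper part.

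None of these points restores 524 as the number of patients with an event in two years.

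**Conclusion.** The two-year event count in section 13.1 is miscomputed. Risk is converted to a hazard, and the hazard is then multiplied by person-time from which no patient is removed at an event. Consistent use of the protocol's own rate gives about 461 patients (95% about 424–498). The stated centre is about 14% too high, or 9% against the 24% end of the cited occurrence. Values above 498 have no support at the stated rate, nor values above about 518 even at 24%.

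This rests on a constant hazard, no loss to follow-up, no competing death and the same rate for either endpoint. The 23%–24% is taken from the protocol and was not checked against the cited trial. The arithmetic is certain; the consequence is modest. The study is exploratory, its size is not derived from this count, and about 460 events may still suffice.

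**What to change.** Restate the last part of section 13.1:

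- Give the expected number of patients with a first event as N × (1 − e^(−rate × time at risk)): about 461 of 2,000 over two years at 13.1 per 100 person-years (95% about 424–498).
- Add that both endpoints count only from week 12, so the 84 weeks to week 96 give about 380 in 2,000 patients before exclusions from the efficacy analysis set.
- Add that follow-up to the simultaneous outcome survey brings further events, depending on the length of registration, so the final total may still reach the range now stated.
- Say that the source's renal definition differs from the trial's composite in both directions, so its rate is not directly transferable and the net direction is unknown.

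The cost is a change of text. One planning figure becomes less favourable; the sample size, endpoints and analyses stay as they are.
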